##### Construct validity

For concurrent validity, we will examine the associations using Pearson correlation coefficients between the PCSS and the total and subscale scores of the PedsQL and PedsQL-SCTM. We will also examine associations between subscales of the PCSS and conceptually relevant items and domains of the PedsQL and the PedsQL-SCTM. We have pre-specified 25 comparisons between PCSS and the PedsQL, and PedsQL SCTM. To control for inflated Type 1 error, we will adjust for multiple comparisons using the Benjamini-Hochberg step-up method. The anticipated pooled sample size of 120 pediatric participants across the designated age cohorts (ages 5–7, 8–12, and 13–17 years) provides adequate precision for two-sided (1–0.05/25) % confidence intervals for Pearson correlation coefficients. With a sample size of 120 pediatric participants, the two-sided 99% confidence interval around a Pearson correlation of 0.8 is 0.70–0.87. Confidence interval calculations are based on a *z* transformation.

To evaluate known-groups validity, we will use independent samples *t*-tests (for two group comparisons), ANOVA (for three or more group comparisons), or Jonkheere-Terpstra tests for differences (for monotonically increasing comparison groups such as those created based on cGVHD severity scores). In evaluating known-groups validity, we will determine if mean item or mean subscale scores differ across relevant indicators of the respondent’s health status, quality of life, or clinical anchors such as NIH cGVHD severity score, NIH cGVHD organ-specific severity scores, and intensity of immunosuppression. Chi-squared tests will also be used to evaluate if the distribution of scores (range 0–4) differs between the known groups. Analysis for a clinical anchor will not be undertaken if it is observed prevalence is <20 or > 80%.

To evaluate the construct validity of the response scales, we will confirm the monotonicity of the PCSS response choices by comparing mean PedsQL total scores across subgroups with worsening PCSS item level scores using Jonckheere-Terpstra tests for differences. We will also plot mean PedsQL total scores across the response choices for each item in the PCSS. We will summarize the proportion of PCSS items where we observed monotonically decreasing mean PedsQL scores across response choices that indicate more symptom severity (higher PedsQL scores reflect better quality of life, and thus as symptom severity increases, it is expected that PedsQL scores will decline).

Given that cGVHD requiring prolonged systemic immunosuppression has an overall incidence of <20% in pediatric transplant survivors (range 5–65% incidence), we anticipate that it will prove challenging to accrue a sufficiently large sample of children to permit stratified psychometric analyses within each age cohort. Accordingly, we plan to pool data across age cohorts for the primary analysis. Sensitivity analyses will be conducted to compare results of pooled analyses with those obtained in the age-specific subgroups, thus identifying age-related trends. As described above, for the primary analysis only, *p* values will be adjusted for multiple comparisons using Benjamini-Hochberg step-up method (Keselman et al., 2002).

Prior to the primary analysis, histograms, descriptive statistics (mean, standard deviation, median, range), box plots, and or normal Q-Q plots will be reviewed for each item to identify drastic departures from normality. Data transformations and/or non-parametric methods (e.g., Wilcoxon rank sum tests and Spearman correlations) will be employed throughout should data appear highly non-normal.

We will also explore the congruence between symptom ratings provided by children and their caregiver-proxies, and examine the subscale structure using confirmatory factor analysis in children (pooling data across age cohorts to achieve a sufficiently large sample for the factor analysis). To evaluate child and caregiver-proxy congruence between symptom ratings, we will use weighted kappa with 95% confidence intervals to estimate the item-level agreement between the child’s severity rating and their caregiver-proxy’s severity rating for each symptom. Sensitivity analyses will compare the results of these pooled analyses with those derived from analyses within age cohorts, thus identifying age-related trends. Confirmatory factor analysis (CFA) will be used to explore the factor structure of the PCSS, based on the 10 domain constructs (skin, eyes, mouth, eating/digestion, lungs and breathing, muscles and joints, urogenital, energy, body image, and mood) hypothesized to underlie the PCSS. Fit indices [specifically root-mean-squared error of approximation (RMSEA), comparative fit index (CFI)] will be used to test the adequacy of the fit of the hypothesized 10-factor model to the observed data. Good model fit is indicated by RMSEA values <0.09 and/or CFI values greater than 0.90. The project sample size of 120 child respondents is likely too small to provide definitive results using CFA, however results will be informative toward the interpretability of subscale scores and will provide power estimates for a future definitive study powered to provide a robust evaluation of the PCSS factor structure.

To inform the comparability of the PCSS and the LSS which is currently used with persons aged 16 years or older, respondents between the ages of 13 and 17 will complete both measures. We will use weighted kappa to estimate agreement between PCSS responses and responses to corresponding items from the LSS, in children between the ages of 13 and 17 and their caregiver-proxies. While this does not substitute for a full psychometric test of the equivalence of both versions, results will provide initial empiric estimates of the lowest age at which younger adolescents can meaningfully complete the LSS, and preliminary information about the comparability of PCSS and LSS values which may be useful toward justifying pooled analyses or interpreting outcomes specifically in trials of new cGVHD therapies when both the PCSS and the LSS are used. In subgroup analysis of respondents ages 13–17, we will examine the congruence between their symptom endorsement rates and their symptom severity ratings on the items of the PCSS and corresponding items in the LSS. This will inform our knowledge of the comparability of both measures in younger and older adolescents and derive preliminary estimates of the lowest age at which young adolescents can meaningfully complete the LSS.

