**Caregiver-proxy (all age groups)**			
Caregiver-proxy PCSS	X	X	X
Caregiver Peds QL Proxy	X	X	X
Caregiver Peds QL Transplant Module Proxy	X	X	X

^*^There is no child report version of the Peds QL Stem Cell Transplant Module validated for children ages 5–7. Caregivers of children ages 5–7 will complete the Caregiver Peds QL Transplant Module Proxy.

Child participants and their caregiver-proxies will receive phone and/or e-mail reminders to log into their unique survey interface to complete required study measures. To minimize missing data, completeness will be monitored prospectively by the study team. Back-up data collection procedures will be implemented for participants who do not complete their scheduled measures.

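### The precision statement names a 99.8% confidence level but illustrates it with a 99% interval at n = 120, and child-report transplant-module correlations can use at most 80 children

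*Protocol article*

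**What the plan says.** The Construct validity section of the protocol article plans Pearson correlations "between the PCSS and the total and subscale scores of the PedsQL and PedsQL-SCTM". It fixes their number: "We have pre-specified 25 comparisons between PCSS and the PedsQL, and PedsQL SCTM". The sample is described as "The anticipated pooled sample size of 120 pediatric participants across the designated age cohorts", and the article says that it "provides adequate precision for two-sided (1–0.05/25) % confidence intervals for Pearson correlation coefficients". The worked figure follows at once: with 120 children, "the two-sided 99% confidence interval around a Pearson correlation of 0.8 is 0.70–0.87". The method is named: "Confidence interval calculations are based on a *z* transformation".

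Table 1 sets Phase 2 enrolment at 40 dyads in each of the three age bands. Table 3 schedules the child-report transplant module for ages 8–12 and 13–17 only, and its footnote gives the reason: "There is no child report version of the Peds QL Stem Cell Transplant Module validated for children ages 5–7". For ages 5–7 the module is completed by the caregiver. Table 3 lists the proxy version of the module for caregivers in all age groups.

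**The concern.** Two things do not fit together.

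- **Level.** The claim is made at one confidence level and supported at another. Dividing 0.05 by 25 gives 0.002, so the named level is 99.8%. The illustration is at 99%.
- **Sample.** The illustration uses all 120 children. Part of the pre-specified set involves the transplant module, and the youngest band does not self-report on it.

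Both mismatches make the stated precision look better than it is. This matters because construct validity is part of the Phase 2 primary objective and this interval is the only computed precision figure offered for the Phase 2 sample. The Reliability section gives an ICC threshold but no interval width, and the factor-analysis text concedes that the sample is probably too small for definitive results. A reader would conclude that an observed correlation of 0.8 excludes values below 0.70. At the article's own level it does not.

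**Working it through.** **Inputs**

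- Comparisons: 25 (Construct validity).
- Named level: 1 − 0.05/25 = 1 − 0.002 = 0.998, so the two-sided critical value is 3.090.
- Illustrated level: 99%, critical value 2.576.
- Correlation: r = 0.8 (Construct validity).
- n = 120 pooled children (Construct validity). For child-report transplant-module scores, n = 40 + 40 = 80 (Tables 1 and 3). Both assume full accrual and no missing data.

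**Formula.** Fisher z interval: tanh[ atanh(r) ± c / √(n − 3) ], where c is the critical value. Here atanh(0.8) = 1.0986, and the standard error is 1/√117 = 0.0925 for n = 120 and 1/√77 = 0.1140 for n = 80.

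**Reproducing the article's figure.** With 99% and n = 120, c × SE = 2.576 × 0.0925 = 0.238. The z-scale limits are 0.860 and 1.337, which transform back to 0.697–0.871. This rounds to 0.70–0.87, so the printed interval is right for its label.

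**At the named level and the available samples (r = 0.8)**

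| Level | n | Interval | Width | Width relative to the 99%, n = 120 interval |
|---|---|---|---|---|
| 99% (as printed) | 120 | 0.697–0.871 | 0.174 | – |
| 99.8% (as named) | 120 | 0.671–0.882 | 0.211 | 0.211/0.174 = 1.21 |
| 99% | 80 | 0.667–0.884 | 0.217 | 0.217/0.174 = 1.25 |
| 99.8% | 80 | 0.633–0.896 | 0.263 | 0.263/0.174 = 1.51 |

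The 99.8% interval at n = 120 and the 99% interval at n = 80 both round to 0.67–0.88. That is coincidence.

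**Could rounding or a variant formula explain the printed figure at 99.8%?** No. Replacing n − 3 by n, n − 1 or n − 2 gives at best 0.673–0.881 at 99.8% with n = 120. An interval that rounds to 0.70–0.87 at 99.8% needs between 168 and 197 children.

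**A smaller correlation.** The article gives only r = 0.8. Taking r = 0.5 as an assumption, the interval is 0.302–0.657 (99%, n = 120), 0.258–0.683 (99.8%, n = 120) and 0.195–0.717 (99.8%, n = 80). The loss in absolute width is larger than at r = 0.8.

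**The case against.** The strongest reply is that nothing was miscalculated and no one is deceived: the 99% label is printed beside the interval, and the figure is correct for it. That stands. A reader might infer an arithmetic error from the mismatch, and there is none. The fault is that the figure is offered as support for a different, stricter level.

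A second reply is that the effect is small. At n = 120 the lower limit falls by about 0.03 and the upper limit rises by about 0.01. The article sets no precision threshold for these correlations, and no test or decision rule depends on the interval. That also stands. A reader might infer that 120 children are too few, or that the claim of adequate precision is false. The article gives no criterion by which to say so.

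Third, a reader might infer that every transplant-module comparison is limited to 80. The documents do not support this. Caregivers of all age groups complete the proxy version, so proxy-report correlations can use up to 120, and the generic PedsQL is self-reported in all three bands. The article does not say how many of the 25 comparisons use child-report transplant scores, or whether proxy scores would stand in for ages 5–7. It may leave both to a fuller document. What remains is that the precision is stated for 120 children only, while child self-report on this module cannot exceed 80.

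Finally, a reader might see a conflict between a 0.05/25 level and the plan that "we will adjust for multiple comparisons using the Benjamini-Hochberg step-up method". That does not hold up. The article speaks of inflated Type 1 error without claiming family-wise control, and 0.05/25 is also the strictest step of the Benjamini-Hochberg procedure with 25 comparisons. It can therefore serve as a conservative planning level.

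**Conclusion.** The inconsistency is real and of moderate severity. The stated 0.70–0.87 is a correct 99% interval for 120 children, but it supports neither the named 99.8% level (0.67–0.88, about 21% wider) nor child-report transplant-module correlations at that level (0.63–0.90, about 51% wider). The 51% combines two effects, the level and the smaller sample, and applies only to that subset of comparisons.

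The results rest on r = 0.8 as in the article, the Fisher z method it names, 40 children per band, and complete data. Missing data would widen the intervals further. The article does not settle whether 99.8% or 99% was intended, so the correction must allow for either.

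**What to change.** Choose one level and make the sentence and the figure agree.

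- **If 99.8% is intended:** write the level as 100 × (1 − 0.05/25)% = 99.8%. State that with 120 children the interval around a correlation of 0.8 is 0.67–0.88, and that for child-report transplant-module correlations (ages 8–17, n = 80) it is 0.63–0.90.
- **If 99% is intended:** remove the 0.05/25 level, say why 99% was chosen, keep 0.70–0.87 for n = 120, and add 0.67–0.88 for child-report transplant-module correlations (n = 80).

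In either case, say which of the 25 comparisons use child-report transplant-module scores, so that the reader knows which interval applies. The cost is a few restated figures, slightly less favourable than those printed. No participants, assessments or analyses are added.

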**Phase 1:** Content validation	Children and adolescents ages 5–17 years	Cognitive debriefing interviews	Age 5–17 years	Evidence of malignant disease relapse including molecular relapse or minimal residual disease (patients with mixed chimerism are eligible to participate)	Children age 5–7 years: *N* = 20 patient-caregiver dyads Children age 8–12 years: *N* = 20 patient-caregiver dyadsChildren age 13–17 years: *N* = 20 patient-caregiver dyads	One time interview with each patient/caregiver dyad	To use cognitive interviewing techniques to evaluate three age-appropriate versions of a new measure of cGVHD symptom bother with respect to item-level comprehension and clarity of the symptom terms, understanding of ‘symptom bother’, and the comprehension and ease of judgment of the response choices and recall period	Prior receipt of allogeneic hematopoietic stem cell transplantation
			Clinical diagnosis of cGVHD				
			Currently, receiving systemic treatment for cGVHD (including phototherapies), or has tapered systemic therapy for cGVHD to discontinuation within the past 12 months				
			English speaking				
			Absence of severe cognitive or psychiatric disability that would impair the child’s capacity for participation or completion of study related procedures, in the judgment of the investigators				
			Caregiver-proxies of participating children		Age older than 18 years				
	Caregiver-proxy of participating subject								
	Able to speak, read, write English								
	**Phase 2:** Psychometric properties		Children and adolescents ages 5–17 years	Quantitative evaluation of measurement properties (construct validity, factor structure, test–retest reliability, and responsiveness to change)	Age 5–17 yearsPrior receipt of allogeneic hematopoietic stem cell transplantationClinical diagnosis of chronic GVHD			Evidence of malignant disease relapse including molecular relapse or minimal residual disease (patients with mixed chimerism are eligible to participate)	Children age 5–7 years: *N* = 40 patient-caregiver dyads	T1 (baseline at enrollment)	Evaluate test–retest reliability, construct validity, and responsiveness of the symptom scale in association with clinical cGVHD characteristics and the Peds QL and PedsQL Stem Cell Transplant Module.			

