Currently receiving systemic treatment for cGVHD (including phototherapies), or has tapered systemic therapy for cGVHD to discontinuation within the past 12 months					Children age 8–12 years: *N* = 40 patient-caregiver dyadsChildren age 13–17 years: *N* = 40 patient-caregiver dyads	T2 (24–48 h after enrollment)T3 (3 months after enrollment)	Congruence between symptom ratings provided by child participants and their caregiver-proxies will be explored.In subjects ages 13–17, we will also compare responses on the PCSS with those from the LSS, to determine the youngest age at which adolescents respondents can comprehend the LSS.				
English speaking											
Absence of severe cognitive or psychiatric disability that would impair the child’s capacity for participation or completion of study related procedures, in the judgment of the investigators								
Caregiver-proxies of participating children		Age older than 18 years						
		Caregiver-proxy of participating subject						
		Able to speak, read, and write English						

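### Setting pooled results beside results from age bands of 40 does not compare the bands with each other, so chance differences can be read as age-related trends

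*Protocol article*

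**What the plan says.** Under Construct validity in the Phase 2 statistical analysis, the article expects that enough children for analyses within each age cohort will be hard to accrue, and so pools the cohorts for the primary analysis. It continues: "Sensitivity analyses will be conducted to compare results of pooled analyses with those obtained in the age-specific subgroups, thus identifying age-related trends". The next sentence confines the multiplicity adjustment to the primary analysis, where p "values will be adjusted for multiple comparisons using Benjamini-Hochberg step-up method". Later in the same section, on child and caregiver-proxy agreement by weighted kappa and on factor structure, it repeats the approach: "Sensitivity analyses will compare the results of these pooled analyses with those derived from analyses within age cohorts, thus identifying age-related trends".

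Table 1 sets the Phase 2 band sizes: "Children age 5–7 years: *N* = 40 patient-caregiver dyads", and likewise 40 dyads at ages 8–12 and 40 at ages 13–17. The number of planned correlations is also stated: "We have pre-specified 25 comparisons between PCSS and the PedsQL, and PedsQL SCTM". No interaction, heterogeneity or trend test by age is named.

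**The concern.** Both sentences name a procedure and state what it delivers. The procedure sets a result from 120 children beside results from 40 of those same children. The two are not independent, and they differ in precision and in significance simply because of sample size. A trend with age is a statement about how the bands differ from each other, and the procedure makes no such comparison. The same unadjusted reading is repeated over up to 25 correlations and over every item-level kappa.

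Age matters in this study: the aims include finding the youngest age at which the scale can be understood, and the primary analysis rests on pooling ages 5–17. A chance pattern across bands could be reported as evidence that the scale performs better or worse at certain ages.

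**Working it through.** **Inputs.** Pooled n = 120, bands of 40 and 25 comparisons come from the article (Table 1; Construct validity). It states the interval method: "Confidence interval calculations are based on a *z* transformation". The true correlation is my assumption, taken from 0.3 to 0.8. The article gives only 0.8, as a precision example.

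**1. The article's own figure.** It states: "With a sample size of 120 pediatric participants, the two-sided 99% confidence interval around a Pearson correlation of 0.8 is 0.70–0.87". Fisher z: atanh(0.8) = 1.0986 and 2.576/√117 = 0.238. Then tanh(0.8605) = 0.697 and tanh(1.3367) = 0.871. The figure is reproduced.

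**2. The same formula in one band.** With n = 40 the standard error of z is 1/√37 = 0.164. The 95% intervals are 0.65 to 0.89 at r = 0.8, 0.22 to 0.70 at r = 0.5, and −0.01 to 0.56 at r = 0.3.

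**3. Chance patterns when all three bands share one true r.** Power per band is p = Φ(√37·atanh(r) − 1.96). Some but not all bands reach p < 0.05 with probability 1 − p³ − (1 − p)³. At r = 0.4, √37 × 0.4236 = 2.577, so p = Φ(0.617) = 0.731, and 1 − 0.391 − 0.019 = 0.59. The gaps between highest and lowest band come from simulating three independent bivariate-normal bands of 40 (100,000 replicates per value).

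| True r (same in all bands) | Median gap | Gap ≥ 0.20 | Some but not all bands p < 0.05 |
|---|---|---|---|
| 0.3 | 0.23 | 60% | 75% |
| 0.4 | 0.22 | 55% | 59% |
| 0.5 | 0.19 | 47% | 23% |
| 0.6 | 0.16 | 36% | 4% |
| 0.8 | 0.09 | 6% | about 0% |

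The last column uses the formula; the simulation gave 75%, 57%, 21%, 3% and 0%.

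**4. Apparent gradients.** With no age effect the six orderings of three equal-sized bands are equally likely, and two of them are monotone: 2/6 = one third, whatever r is (simulated 0.33 throughout). If all 25 comparisons had three bands, 25/3 ≈ 8 would show a steady gradient by chance. This is an upper figure. The footnote to Table 3 says there is no child-report transplant module for ages 5–7, so child-report comparisons with that module have two bands and at most 80 children. The article does not say how the 25 divide.

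**5. What a direct test would do.** Take Q = 37·Σ(z_j − z̄)² on 2 df. Its simulated false-positive rate was 4.9% to 5.2% per comparison for true r from 0.3 to 0.8. Unadjusted, 25 independent tests would still give at least one false positive with probability 1 − 0.95²⁵ = 0.72. Power before adjustment is 57% for band correlations 0.3/0.5/0.7 and 16% for 0.4/0.5/0.6 (linear trend on 1 df: 67% and 21%). For two bands, 80% power needs a z difference of (1.960 + 0.842)·√(2/37) = 0.65, for example 0.80 against 0.42.

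**The case against.** The strongest reply is that an article may leave the method of comparing subgroups to a fuller plan, that these are labelled sensitivity analyses, and that leaving such analyses unadjusted is common. The article also concedes in its Discussion that sparse data may hide findings within an age group. Part of this stands: a fuller plan may contain a test, and the pooled primary inference is not touched. But the article is not merely silent. It says twice that the pooled-versus-band comparison identifies age trends. Its concession concerns missed findings, not spurious ones.

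Three stronger readings might be inferred, and the document does not support them.

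- **That bands will be judged by which reach p < 0.05.** No such rule is stated. Much of the surrounding text concerns estimation, and kappas are to carry 95% intervals. The last column of the table matters only if someone reads the results that way.
- **That the bands will usually appear to differ.** On mixed significance this holds only for weak true correlations. The figure is 23% at 0.5 and negligible at 0.8.
- **That this is the only evidence on age suitability.** Phase 1 sets an 80% item-comprehension criterion within each band and a stopping rule for ages 5–7, and considers whether only proxy report should be recommended there.

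**Conclusion.** The point holds in a limited form. The procedure that the article fixes cannot support the conclusion attached to it, and chance differences can be read as age effects. The one-third rate of steady gradients does not depend on the true correlation, but applies only where there are three bands. The size of the gaps does depend on it: a median of about 0.2 for assumed correlations of 0.3 to 0.5, and 0.09 at 0.8. The calculations assume bivariate normal scores and full bands of 40. They were done for correlations; the kappas share the logic but were not computed. The consequence is confined to statements about age. It is worth correcting because age is among the study's aims.

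**What to change.** - Base any statement of an age trend on a direct between-band comparison: an age-by-measure interaction in the pooled model, or a Fisher-z homogeneity test. Use three bands, or two for child-report transplant-module comparisons. Apply Benjamini-Hochberg across these tests.
- For correlations and kappas alike, report band estimates and between-band differences with confidence intervals.
- In both sentences, replace the claim that trends will be identified with wording that calls age patterns exploratory.
- Note that ages 5–7 answer on a three-point scale, while older children and proxies use five points, so a difference in that band may reflect the instrument.

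The cost is a few sentences and one added analysis, with no new data. The drawback is low power: at 40 per band only large age differences can be confirmed. The report should say so, and should not take a non-significant test as support for pooling.

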## Methods and analyses

### Phase 1: establish content validity of the candidate items through cognitive interviewing

#### Design, sample, and setting

A 10-domain structure (Figure 1) and an initial pool of 50 items were constructed based on our prior concept elicitation study (Wiener et al., 2014). The PCSS (both child and caregiver-proxy versions) evaluates how much the child has been bothered by each symptom in the past 1 month. The 1 month recall period and the focus on the concept of symptom bother align the PCSS with the LSS, the measure used with respondents ages 18 and older. Symptom bother incorporates symptom frequency, severity, and interference with usual activities (Gawlicki et al., 2014). Responses are provided on a three-point scale incorporating a pictogram (for respondent’s ages 5–7 years) or a five-point Likert scale (for children ages 8–17 and caregiver-proxy respondents).

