Data are analyzed after every five interviews, and cumulative item-by-item determinations of both comprehension and saturation, stratified by age band, are documented in a coverage and saturation matrix (Kerr et al., 2010; Tomlinson et al., 2016; Meadows, 2021). Each transcript is mapped back to each PCSS item and a cumulative summary of the findings for each item and next steps (i.e., revise and retest, comparatively test a revision, continue testing, saturation achieved, and eliminate item from item pool) is constructed for each item and organized in Microsoft Excel. This approach also ensures that all PCSS items receive a comparable extent of probing across interviews within each age band and identifies the timepoint at which no new information about an item is being generated by the interviews.

Each PCSS item is debriefed with at least five children within each age band. Cognitive interviews are normally based on intensive interviewing in relatively small samples (Willis et al., 2005; Willis, 2005, 2015). Approximately 5–8 participants per item and per age group is a general rule of thumb to achieve saturation with cognitive interviews (Kerr et al., 2010; Hennink et al., 2017) since the type of logical and structural problems that we wish to identify are relatively independent of sample size (Miller et al., 2014). Symptom terms eliciting confusion or demonstrating misinterpretation by three or more respondents within an age band are considered for revision. Interview scripts are slightly refined to accommodate these changes to PCSS items.

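### At 120 children the planned 10-factor CFA has up to 145 free parameters, and its RMSEA and/or CFI rule does not reliably separate a correct structure from a wrong one, although the fit is to inform how subscale scores are interpreted

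*Protocol article*

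**What the plan says.** The factor-analysis paragraph under Construct validity (Phase 2, Statistical analysis) describes a single model of ten domains in child respondents, "pooling data across age cohorts to achieve a sufficiently large sample for the factor analysis". Two fit indices, RMSEA and CFI, "will be used to test the adequacy of the fit of the hypothesized 10-factor model to the observed data". The criterion is: "Good model fit is indicated by RMSEA values <0.09 and/or CFI values greater than 0.90". The article does not say whether 'and' or 'or' decides, names no estimator, and mentions no rival, reduced or domain-level model.

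The same paragraph concedes: "The project sample size of 120 child respondents is likely too small to provide definitive results using CFA". It continues: "however results will be informative toward the interpretability of subscale scores", and adds that the results will supply power estimates for a later study.

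On the number of items, the Phase 1 section Design, sample, and setting says "an initial pool of 50 items were constructed based on our prior concept elicitation study". One possible outcome for an item in the Phase 1 Data analysis section is "eliminate item from item pool", so the Phase 2 scale may be shorter; its length is not given. On response format: "Responses are provided on a three-point scale incorporating a pictogram (for respondent’s ages 5–7 years) or a five-point Likert scale" for older children and caregivers.

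**The concern.** A model of this size has about as many free parameters as there are children, or more. In that situation the maximum-likelihood chi-square runs high even when the model is exactly right. The two indices react differently. CFI compares the excess with the misfit of the independence model, so it falls when loadings are modest. RMSEA spreads the excess over a very large number of degrees of freedom, so it stays small almost whatever the structure.

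At stake is the use the article keeps for the result. A CFI below 0.90 could be read as evidence against the ten domains when it mainly reflects items per child. An RMSEA below 0.09 could be read as support for them when a single general factor might have passed as well.

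**Working it through.** **The plan's own figure.** No sample size, power or parameter count is given for the CFA. The only calculation for N = 120 is the 99% interval for a Pearson correlation of 0.8. It reproduces: atanh(0.8) = 1.0986; half-width 2.5758/√117 = 0.2381; tanh(0.8605) = 0.697 and tanh(1.3367) = 0.871, against the stated 0.70–0.87. It says nothing about the CFA.

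**Model size.** For p items on ten correlated factors with simple structure, free parameters are p loadings + p residual variances + 10×9/2 = 45 correlations, that is 2p + 45. Degrees of freedom are p(p+1)/2 minus that count.

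| Items | Parameters | df | Children per parameter |
|---|---|---|---|
| 50 | 145 | 1275 − 145 = 1130 | 120/145 = 0.83 |
| 40 | 125 | 820 − 125 = 695 | 120/125 = 0.96 |
| 30 | 105 | 465 − 105 = 360 | 120/105 = 1.14 |

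**What the cut-offs mean at N = 120.** RMSEA = √[(T/df − 1)/(N − 1)], so RMSEA <0.09 is met whenever T/df < 1 + 119 × 0.09² = 1.96. CFI = 1 − (T − df)/(T₀ − df₀), where T₀ is the independence-model chi-square. In simulation the correct 50-item model with normal items had mean T/df of about 1.195. RMSEA is then √(0.195/119) = 0.040, far inside the limit. The excess is 0.195 × 1130 = 220, so CFI >0.90 needs T₀ − df₀ above about 2,200, which modest loadings do not supply.

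**Simulation of the exactly correct model.** Assumptions, because the article does not give these: equal items per domain, uncorrected maximum likelihood, factor correlation 0.3 unless noted, and either normal items or skewed five-category items (about half zeros) treated as continuous. There were 100 replicates per row, so the simulation standard error is about 5 points at mid-range.

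| Items, loading | CFI >0.90, correct model | RMSEA <0.09, correct model | RMSEA <0.09, wrong one-factor model |
|---|---|---|---|
| 50, 0.5, normal | 1% | 100% | 100% |
| 50, 0.6, normal | 8% | 100% | 100% |
| 50, 0.7, normal | 56% | 100% | 0% |
| 50, 0.7, normal, correlation 0.5 | 72% | 100% | 81% |
| 50, 0.8, normal | 100% | 100% | 0% |
| 50, 0.7, skewed | 0% | 100% | 15% |
| 50, 0.8, skewed | 14% | 100% | 0% |
| 40, 0.7, normal | 92% | 100% | 0% |
| 30, 0.6, normal | 73% | 100% | 99% |
| 30, 0.7, normal | 99% | 100% | 0% |

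The mean CFI of the wrong one-factor model in these rows was 0.31–0.58, so CFI did separate it from the correct model.

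A second set of runs with skewed items (60 replicates, factor correlation 0.4, loadings 0.6–0.8) gave CFI >0.90 in 0–12% with 50 items, 2–65% with 40 and 25–97% with 30. A third, smaller set (25 replicates per setting, 50 items) gave 0–4% for skewed items, and 4%, 56% and 100% for normal items at loadings 0.6, 0.7 and 0.8. With a small-sample-corrected chi-square, CFI >0.90 was then met in 100% for normal items and 32–92% for skewed ones.

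**Domain-level models.** A five-item one-factor model has 10 parameters (12 children per parameter) and 15 − 10 = 5 df. A four-item model has 8 parameters and 2 df. A three-item model has 6 parameters for 6 moments and no testable fit. For correct five-item models CFI >0.90 was met per domain in 94–100%. RMSEA is a poor judge here. With 5 df the cut-off is T < 5 × 1.964 = 9.82, which a correct model meets with probability 0.92; with 2 df it is T < 3.93, probability 0.86. Simulation gave about 77–92%, the lower values with skewed items.

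**The case against.** The strongest reply is that the article does not oversell this analysis. It calls the CFA exploratory, says that 120 is likely too small and points to a later, properly powered study. That stands, and it limits the point to the use still claimed for the fit.

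A reader might infer that the plan's rule will usually reject the true ten-domain structure. The documents do not support that. The rule is worded 'and/or', and under 'or' the correct model passed on RMSEA in every run. Fifty is the item pool before Phase 1, not the Phase 2 count. With loadings of 0.8 and normal items, or with about 30 items at 0.7, the CFI problem nearly disappears. The figures also presume uncorrected maximum likelihood, whereas the article names no estimator and allows transformations or non-parametric methods for highly non-normal data. The choice of estimator may properly sit in a fuller document.

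A reader might also infer that the 10-factor model is to be fitted in cohorts of 40, where the covariance matrix has rank at most 39 and is singular with 40 or more items. The sentence on pooled and age-cohort analyses follows the weighted-kappa description and precedes the CFA details, so it may refer to kappa only. It needs clarifying, but it is not an established error.

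Nor are the concurrent and known-groups analyses conditional on CFA fit, and no distortion of the future power estimates has been shown. Finally, separate domain models cannot show that the ten domains are distinct, so they cannot replace the joint model.

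**Conclusion.** The concern holds in a limited form. The size of the model is arithmetic: 105 to 145 free parameters for 30 to 50 items, in 120 children. At that size the two cut-offs give different answers and the text does not say which decides. Uncorrected CFI often misses 0.90 for a correct structure when items are skewed or loadings are about 0.6. RMSEA <0.09 is met essentially always by the correct model. A wrong one-factor model also meets it when loadings are 0.5–0.6, or at 0.7 with factor correlation 0.5, but rarely or never in the other settings tried.

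Skewed items are plausible: the scales have three or five points, and children up to 12 months off systemic therapy are eligible. A pass or fail on this rule therefore cannot carry the stated weight for interpreting subscale scores. The simulated percentages rest on assumed item counts, loadings, factor correlations and estimator, and would change with them.

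**What to change.** In the factor-analysis paragraph under Construct validity:

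- Report the 10-factor model descriptively, with no pass/fail verdict from these cut-offs. Use a small-sample-corrected chi-square (Swain or Bartlett) and an estimator or correction suited to ordinal items.
- Compare it with a simpler rival, such as a one-factor model, so that the fit is read against an alternative.
- Add, alongside the joint model, one-factor models for domains with at least four items and paired-domain models for smaller domains. Report loadings, CFI and inter-domain correlations, and do not judge these low-df models on RMSEA <0.09 alone.
- State that the within-age-cohort sensitivity analyses do not include the 10-factor CFA.

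The cost is a change of analysis wording and a few more model runs, with no change to recruitment or data collection. The small downside is that there is no single overall fit verdict, which the article already says this sample cannot give definitively.
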